## Abstract

**Background:**

In young children, bronchiolitis is the most common illness resulting in hospitalization. For children less than age 2, bronchiolitis incurs an annual total inpatient cost of $1.73 billion. Each year in the United States, 287,000 emergency department (ED) visits occur because of bronchiolitis, with a hospital admission rate of 32%-40%. Due to a lack of evidence and objective criteria for managing bronchiolitis, ED disposition decisions (hospital admission or discharge to home) are often made subjectively, resulting in significant practice variation. Studies reviewing admission need suggest that up to 29% of admissions from the ED are unnecessary. About 6% of ED discharges for bronchiolitis result in ED returns with admission. These inappropriate dispositions waste limited health care resources, increase patient and parental distress, expose patients to iatrogenic risks, and worsen outcomes. Existing clinical guidelines for bronchiolitis offer limited improvement in patient outcomes. Methodological shortcomings include that the guidelines provide no specific thresholds for ED decisions to admit or to discharge, have an insufficient level of detail, and do not account for differences in patient and illness characteristics including co-morbidities. Predictive models are frequently used to complement clinical guidelines, reduce practice variation, and improve clinicians’ decision making. Used in real time, predictive models can present objective criteria supported by historical data for an individualized disease management plan and guide admission decisions. However, existing predictive models for ED patients with bronchiolitis have limitations, including low accuracy and the assumption that the actual ED disposition decision was appropriate. To date, no operational definition of appropriate admission exists. No model has been built based on appropriate admissions, which include both actual admissions that were necessary and actual ED discharges that were unsafe.

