#### Predictive Models

We will use Weka [56] to construct predictive models. Weka is a widely used open-source machine learning toolkit. It integrates a large set of standard machine learning algorithms and feature selection techniques. Both categorical and numerical variables exist in administrative, clinical, and environmental data. Supervised machine learning algorithms that can deal with both categorical and numerical variables, such as *k*-nearest neighbor and random forest, will be used. We will examine each applicable algorithm and tune hyper-parameters manually.

The classic area under the receiver operating characteristic curve (AUROC) [56] performance metric will be used. Our target will be models achieving an AUROC larger than or equal to 0.9, which is considered outstanding discrimination [57]. Some machine learning models, such as decision tree and k-nearest neighbor (ie, similar patients), can be more easily interpreted [58,59]. Other machine learning models, such as random forest, are less straightforward to interpret. If accuracies of models are comparable (AUROC ≥0.9 and ≤0.02 worse for interpretable models compared to less interpretable models), we will favor those that clinicians can more easily interpret.

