#### Sample Size Justification and Performance Evaluation

We have 10 years of data. We will train and test predictive models using a standard method. We will perform stratified 10-fold cross validation [56] on the initial 9 years of data to train predictive models and provide estimates of their accuracy. Data from the tenth year will be used to evaluate performance of the best-performing machine learning algorithm, reflecting use in practice. To figure out the environmental variable, administrative, and clinical attributes necessary for high accuracy, we will use backward elimination [36] to remove input variables so long as the AUROC does not decrease by more than 0.02 or go below 0.9.

No AUROC achieved by current care has been reported before. By extrapolating from statistics reported in the literature (unnecessary admissions up to 29% and unsafe ED discharges of 6%), we anticipate the AUROC achieved by current care to be between 0.6 and 0.8+ [20-24,27]. We will test the hypothesis that the model’s prediction will be more accurate by a difference in AUROC of larger than or equal to 0.05. The dependent variable has 2 possible values: appropriate hospital admission and appropriate ED discharge. Assuming a correlation coefficient of 0.6 between the model’s prediction result and the actual disposition decision for both values and using a 1-sided Z-test at a 0.05 significance level, a sample size of 356 instances per possible value of the dependent variable will have 90% power to detect an AUROC increase of 0.05. Data from the tenth year include 3615 ED visits for bronchiolitis, which provides adequate power for testing our hypothesis.

Based on 2 prior studies’ results, we anticipate that our model will achieve an AUROC larger than or equal to 0.9 and outperform current care in making disposition decisions. Neither prior study on predicting a bronchiolitis patient’s ED disposition is similar to our study, which uses appropriate admission as the gold standard. The first study [21] used actual admission as the gold standard and achieved an AUROC of 0.87. The second study [34] used judgment of an attending pediatrician as well as a length of stay longer than 1 day as the gold standard. The predictive model achieved 81% accuracy, better than an average admitting resident’s disposition decision.

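### The Aim 2 test sets a full-curve model AUROC against the AUROC of a yes/no decision, so a model no better than clinicians at their own operating point can be declared more accurate

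*Protocol article*

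**What the plan says.** Under Aim 2, Predictive Models, the article fixes the metric: "The classic area under the receiver operating characteristic curve (AUROC) [56] performance metric will be used". It sets the goal as well: "Our target will be models achieving an AUROC larger than or equal to 0.9".

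Under Aim 2, Sample Size Justification and Performance Evaluation, the comparator is current care. The article acknowledges that "No AUROC achieved by current care has been reported before" and extrapolates a value from two published error rates, "unnecessary admissions up to 29% and unsafe ED discharges of 6"%. From these it says "we anticipate the AUROC achieved by current care to be between 0.6 and 0.8", with a plus sign after the upper figure. The hypothesis is that the model's "prediction will be more accurate by a difference in AUROC of larger than or equal to 0.05". It is tested by a one-sided Z-test at 0.05, assuming a correlation of 0.6 between the model's result and the actual disposition. The outcome is binary: "The dependent variable has 2 possible values: appropriate hospital admission and appropriate ED discharge". The stated requirement is 356 instances per outcome class for 90% power, and year 10 supplies 3615 visits.

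The Abstract describes what clinicians produce: "ED disposition decisions (hospital admission or discharge to home) are often made subjectively". That is a choice between two actions, not a score. The Aim 2 text gives no model cutoff and no comparison at matched sensitivity or specificity.

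**The concern.** The two AUROCs do not measure the same thing. A yes/no decision has one point on the ROC plot. Joined to the corners, it encloses (sensitivity + specificity)/2. A graded score traces a whole curve. If that curve is strictly concave and passes through the clinicians' point, it lies above the two straight segments and encloses more area. At that point the model and the clinicians have the same sensitivity and specificity, yet the AUROC difference is positive.

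This is the only hypothesis test stated for Aim 2. It carries the expectation that the model will outperform current care, which leads on to the randomized trial proposed in the Introduction. A bias comparable in size to the 0.05 margin, or larger, makes that claim unreliable.

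**Working it through.** **The plan's own figure.** For a paired AUROC Z-test, n per class = (1.645 + 1.282)² × (V1 + V2 − 2 × 0.6 × √(V1·V2)) / 0.05², with the Hanley-McNeil variance V = A/(2−A) + 2A²/(1+A) − 2A². The article gives no base AUROC. Taking 0.70, the middle of 0.6 to 0.8, as an assumption:
- V1 (at 0.70) = 0.1349 and V2 (at 0.75) = 0.1179, so n = 348. Using the null variance for the alpha term gives 360. Both are within 3% of 356.
- Over base values 0.60 to 0.85 the formula gives 421 down to 178.
- If both ratings are treated as yes/no with sensitivity = specificity, V = A(1−A)/2. Then n is 273 at 0.70 and at most 341 (at 0.50), so 356 is not reached.

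The figure of 356 is therefore not in question, and it fits a rating-scale calculation better than a yes/no one.

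**Current care from the article's rates.** The Introduction gives 32%-40% admitted, 20%-29% of admissions unnecessary and 6% of discharges unsafe. At 36% admitted (midpoint) and 29% unnecessary, the shares of all visits are:
- Admitted, appropriate: 0.36 × 0.71 = 0.2556
- Admitted, unnecessary: 0.36 × 0.29 = 0.1044
- Discharged, unsafe: 0.64 × 0.06 = 0.0384
- Discharged, safe: 0.64 × 0.94 = 0.6016

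Sensitivity = 0.2556/0.2940 = 0.869. Specificity = 0.6016/0.7060 = 0.852. AUROC = (0.869 + 0.852)/2 = 0.861.

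**A model that only matches clinicians.** An equal-variance binormal curve through that point has AUROC Φ((z_sens + z_spec)/√2) = Φ((1.124 + 1.046)/√2) = 0.937. The gain is 0.077 with no better decision at that point. Over the full ranges of 32%-40% and 20%-29%, current care is 0.858 to 0.888 and the gain is 0.069 to 0.079.

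**Across the article's anticipated range.** With sensitivity = specificity:

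| Current-care AUROC | Same-point graded AUROC | Gain |
|---|---|---|
| 0.60 | 0.640 | 0.040 |
| 0.65 | 0.707 | 0.057 |
| 0.70 | 0.771 | 0.071 |
| 0.80 | 0.883 | 0.083 |
| 0.85 | 0.929 | 0.079 |

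The gain passes 0.05 at a current-care AUROC of about 0.63.

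**A somewhat worse model.** With care at 0.861, a model at 0.911 shows a gain of exactly 0.05. Its binormal separation is √2 × Φ⁻¹(0.911) = 1.903. At the clinicians' specificity its sensitivity is Φ(1.903 − 1.046) = 0.804, against 0.869. In 3615 visits that is 3615 × 0.294 × 0.196 ≈ 208 missed appropriate admissions, against 3615 × 0.0384 ≈ 139.

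**What the test would do in year 10.** This was simulated with DeLong paired tests, 3615 visits, appropriate-admission prevalence 0.294 and latent correlation 0.6.
- Matching model (0.937): significant against a null of 0 in 100% of runs, and against 0.05 in over 99%.
- Worse model (0.911): significant against 0 in 100% of runs. It was significant against 0.05 in only about 5% to 8%, and the estimated gain reached 0.05 in about 53% to 55%. It sits on the margin.

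**The case against.** The strongest reply is that graded scoring is inferred. The article never says so outright, and in Aim 3 the model's prediction result is plainly a yes/no suggestion. If the model is also dichotomised in Aim 2, the bias disappears. This stands as a limit on certainty. The classic AUROC metric, the 0.9 target, the absence of any cutoff and the way 356 reproduces all favour the graded reading. The text needs a change in either case.

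A reader might infer that a model worse than clinicians will always pass. The document does not support that. It does not say whether the null is a difference of 0 or of 0.05. The worse model always passes only against 0, and rarely against 0.05. At care 0.60 even a matching model gains less than the margin.

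The 0.9 target is a partial safeguard. Under the same binormal assumption, 0.9 corresponds to sensitivity = specificity = 0.818. A model that meets the target is therefore better at its balanced point than care at 0.80 or below. The safeguard fails at the article's own error rates, where care is 0.858 to 0.888 and a model at 0.911 meets both the target and the margin.

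Aim 3 does score the model's yes/no suggestions on cost, ED returns and admissions, and the study is retrospective. That limits the practical consequence, but it does not correct the Aim 2 claim.

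Finally, the sizes depend on an equal-variance binormal curve. The decision trees and k-nearest-neighbor models that the article may prefer have stepped curves, so their gains may differ. The direction needs only strict concavity.

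**Conclusion.** The concern holds in this form: as written, the Aim 2 comparison favours the model, and a model no better than clinicians at their operating point can be declared more accurate. The spurious gain is 0.069 to 0.079 at the article's own rates. With sensitivity = specificity it is 0.040 at a current-care AUROC of 0.60 and exceeds 0.05 from about 0.63. This rests on two assumptions: that the model is scored on its graded output, and that its curve is equal-variance binormal (for the sizes) or strictly concave through the clinicians' point (for the direction). The bias is present whether the null is 0 or 0.05, but its effect on the test result differs as shown above. It should not be read as showing that an inferior model is sure to succeed, or that 356 was miscalculated.

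**What to change.** Set one model cutoff on years 1-9. In year 10, compare the model's yes/no prediction with the actual disposition by the paired difference in (sensitivity + specificity)/2, and report sensitivity and specificity for both. State whether the null is 0 or 0.05, restate the margin and sample size on this scale, and keep the graded AUROC as a descriptive measure.

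McNemar's test of sensitivity alone should not carry the claim. A cutoff chosen on years 1-9 need not give the clinicians' specificity in year 10, and a specificity gap would distort that test.

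Power remains adequate. With V = A(1−A)/2, correlation 0.6 and a null of 0, detecting 0.05 needs 320 per class at base 0.60, 273 at 0.70 and 199 at 0.80. The article's rates imply about 969 to 1287 appropriate admissions in year 10. Even with zero correlation at base 0.60, the need is 8.564 × (0.12 + 0.11375)/0.0025 ≈ 801. A null of 0.05 would need its own calculation.

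The cost is a wording change and one extra cutoff step, with no new data. The apparent advantage over current care will be smaller.

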### Aim 3: Conduct Simulations to Estimate the Impact of Using the Model on Bronchiolitis Outcomes

We will use a method similar to that in Luo et al [46] to establish the model’s utility for future use in clinical practice. More specifically, we will estimate the impact of using the model on bronchiolitis outcomes by applying the model to a retrospective cohort, and determine how the model can be generalized to different sites that collect differing sets of attributes. Our model will be developed using data from Intermountain Healthcare. Our simulations will help determine how to implement the model in other EDs. No prior study has either assessed the impact of using a predictive model on bronchiolitis outcomes or found the set of attributes most essential to generalize the model.

#### Outcomes

We will assess the outcomes of hospital admission, discharge to home, cost, and ED return. The primary outcome is cost. Other outcomes are indirectly reflected in cost and secondary. Each medical claim is companioned by a billed cost, a reimbursed cost, and an Intermountain Healthcare internal cost [52]. The Intermountain Healthcare internal cost [62] will be used because it is subject to less variation resulting from member cost-sharing [52] and more closely reflects actual cost. To deal with inflation, the medical consumer price index [63] will be used to standardize costs to 2014 US dollars. ED returns will be computed using the time interval defining unsafe discharge.

#### Estimate a Model’s Impact

Given a predictive model and a set of input variables, we will estimate the impact of using the model on each outcome. The same method in Aim 2 will be used to train the model on data from the first 9 years. Data from the tenth year have 4 groups: (1) necessary admissions, (2) unnecessary admissions, (3) unsafe discharges, and (4) safe discharges (Figure 1). For each group, we will obtain prediction results, then estimate the outcome if the model’s suggestions were followed. For example, consider necessary admissions. The model will erroneously predict that some of these patients should be discharged. We assume that in clinical application, every such patient will incur an unsafe discharge, an early return visit for bronchiolitis, and a cost equal to unsafe discharges’ average cost. The overall estimated outcome is the aggregate of outcome estimates in all 4 groups. Similarly, we can determine the minimum requirement of the model’s accuracy for the model to be valuable clinically.

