## Methods

Machine learning is a field that studies the automatic improvement of computer algorithms with experience. Machine learning methods—such as support vector machine, neural network, and decision tree—are commonly used in predictive modeling [36] and will be adopted in our study. In comparison to statistical methods, machine learning can improve prediction accuracy, occasionally doubling it, with less stringent assumptions on data distribution [38,42,43].

For all 3 aims, we will use the same patient population and data sets:

Patient population: Our study cohort includes children under age 2 who had ED encounters at 22 Intermountain Healthcare facilities for bronchiolitis (ICD-9-CM discharge diagnosis code 466.1 [4]) in the past 10 years. Intermountain Healthcare is the biggest health care system in Utah, comprising 185 clinics and 22 hospitals.Data sets: A large administrative and clinical data set in the enterprise data warehouse (EDW) of Intermountain Healthcare will be used. The Intermountain Healthcare EDW contains a vast set of attributes [44]. Our Intermountain Healthcare data analyst will run SQL queries to obtain a data set that has been de-identified and encrypted and then securely transfer it to a computer that is encrypted and password-protected. Secondary analysis will be conducted on the computer. Intermountain Healthcare has dedicated tables to identify changes in procedure and diagnosis codes. The data set contains electronic documentation of about 85% of pediatric care delivered in Utah [45] and includes approximately 400 attributes. A partial list of categories of these attributes includes: admission date and time; age; orders (eg, medications, labs, exams, immunizations, imaging, counseling, etc), including order name, ordering provider, performing date, and result date; allergies; chief complaint; diagnoses; discharge date; exam result; facility seen for the patient visit; gender; health insurance; health care cost (billed charge, Intermountain Healthcare internal cost and reimbursed cost); height; home address; immunizations; lab test result; language(s) spoken; medication refills; primary care physician as listed in the electronic medical record; problem list; procedure date; procedures; provider involved in the visit; race/ethnicity; referrals; religion; visit type (inpatient, outpatient, urgent care, or emergency department); vital signs; and weight [46].

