For the last 5 years, data captured cover more than 2900 patients under age 2 and 3500 ED encounters for bronchiolitis per year. Due to its attribute richness and large size, the data set provides many advantages in the exploration of the proposed predictive models. Furthermore, we will use 21 environmental variables that regional monitoring stations recorded over the past decade within the Intermountain Healthcare region. These variables include carbon monoxide, nitrogen dioxide, particulate matter up to 2.5 μm in size and 10 μm in size, ozone, sulfur dioxide, relative humidity, temperature, precipitation, wind speed, dew point, and activities of each of the following viruses: enterovirus; adenovirus; parainfluenza virus types 1, 2, and 3; human metapneumovirus; influenza A and B viruses; rhinovirus; and respiratory syncytial virus. The data for all nonvirus environmental variables came from federal data sources [47,48], which provide such data throughout the United States. Observation unit admissions will be treated as hospital admissions since the only pediatric observation unit within Intermountain Healthcare has the same admission, coding, billing, and documentation requirements. Our analysis will consider various attribute combinations to ascertain the minimum requirement on performance and will permit tradeoffs for the adaption of our model beyond our setting dependent upon available attributes. Our analysis results will serve as the basis for future expansion of our models to other clinical data sets and diseases beyond bronchiolitis.

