### Aim 1: Develop an Operational Definition of Appropriate Hospital Admission for ED Patients with Bronchiolitis

In a recent paper [39], we provided a definition framework of appropriate hospital admissions. As shown in Figure 1, we equate appropriate admissions to necessary admissions and unsafe discharges. We equate appropriate ED discharges to safe discharges and unnecessary admissions. The definition uses several threshold values, such as the maximum number of hours for which major medical interventions are used. Using a data-driven approach, we will fill in these values and develop an operational definition to be used in Aims 2 and 3.

For unsafe discharges, we will examine the distribution of the interval between discharge from the ED and a return visit resulting in admission for bronchiolitis within the period of 2 weeks [49,50]. The 95th percentile of the interval will cover most readmissions and define the return threshold for unsafe discharge. The distribution is highly skewed toward a short interval [27]. Thus, the return threshold will be insensitive to the length of the period chosen.

For unnecessary admissions, we will examine the patients who stayed in the hospital for 12 hours or less and were discharged without readmission for bronchiolitis within 2 weeks. These patients are likely to have been admitted unnecessarily. Their median duration of using major medical interventions (Figure 1) will serve as a conservative threshold for use of major medical interventions in all admissions. Unnecessary admissions are those with major medical intervention exposures for no longer than the threshold. We will conduct sensitivity analysis to evaluate the impact of interactions between major medical interventions and other variables.

If the operational definition for all bronchiolitis patients lacks face validity, we will examine data distributions for different age groups to obtain operational definitions by age group. Since the medical interventions for bronchiolitis have not changed over the last 10 years, we would expect the operational definition to remain the same during this period.

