#### Sample Size Justification and Performance Evaluation

We will test 3 hypotheses: use of our predictive model will be linked to reduced (1) costs, (2) ED returns, and (3) hospital admissions. Due to their skewed distribution, cost data will be log-transformed [52]. The primary hypothesis will be accepted if the model lowers the log cost by at least 10% of its standard deviation. We will use 1-sided paired-sample t-test to assess the log cost difference between the model’s prediction result and the actual disposition decision. We will use McNemar’s test to assess the difference in ED returns and hospital admissions. A sample size of 857 data instances has 90% power to support the primary hypothesis at a 0.05 significance level. Data from the tenth year include 3615 ED visits for bronchiolitis, which offers sufficient power for testing the primary hypothesis.

If performing simulations on 1 computer is too slow for the numerous combinations of attribute groups, we will conduct parallel simulations on the secure Homer computer cluster [60].

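### Aim 3 simulates by ED visit and has no step to drop a return visit once the model admits at the first visit, which biases the secondary admissions comparison against the model

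*Protocol article*

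**What the plan says.** The cohort in the protocol article's Methods is "children under age 2 who had ED encounters at 22 Intermountain Healthcare facilities for bronchiolitis", with no restriction to a first or index visit. Methods adds that in the last 5 years "data captured cover more than 2900 patients under age 2 and 3500 ED encounters for bronchiolitis per year", so repeat visits are in the data.

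Aim 1 identifies unsafe discharges from "the interval between discharge from the ED and a return visit resulting in admission for bronchiolitis within the period of 2 weeks". The 95th percentile of that interval becomes the return threshold.

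In Aim 3, Estimate a Model's Impact, the year-10 data are divided into necessary admissions, unnecessary admissions, unsafe discharges and safe discharges. An outcome is estimated for each group as if the model had been followed, and then: "The overall estimated outcome is the aggregate of outcome estimates in all 4 groups". One case is worked through: a necessary admission that the model wrongly discharges is given an early return and the average cost of unsafe discharges. The reverse case, an unsafe discharge that the model would admit, is not described.

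Aim 3, Sample Size Justification and Performance Evaluation, compares the model's prediction with the actual disposition, using a one-sided paired t-test on log cost (primary) and McNemar's test on ED returns and admissions. It counts the units as visits: "Data from the tenth year include 3615 ED visits for bronchiolitis, which offers sufficient power for testing the primary hypothesis".

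**The concern.** An unsafe discharge and its return admission are two rows but one illness episode, and the second row depends on the first. If the model admits the child at the first visit, the return would not take place. A sum over visits changes the first row from discharge to admission and leaves the second row as an admission. Current care then shows one admission for the episode and the simulation shows two, where the real alternative has one.

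The admissions hypothesis is thus charged for the patients in whom the model corrects an unsafe discharge. For cost, the primary outcome, the result depends on whether an unsafe discharge's cost contains the return stay. The article leaves this open, although the same quantity prices the model's own wrong discharges.

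**Working it through.** **The plan's own figure.** n = ((z₀.₉₅ + z₀.₉₀)/0.10)² = ((1.645 + 1.282)/0.10)² = 856.4, rounded up to 857. The stated sample size reproduces and is not in question.

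**Inputs.** 3615 visits (Aim 3). From the Introduction: 32% to 40% admitted, 20% to 29% of admissions unnecessary, 6% of ED discharges unsafe. These are literature rates, not study data, and are applied here to visits.

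**Return admissions in year 10.**
- 32% admitted: 3615 × 0.32 = 1157 admissions, 2458 discharges; 0.06 × 2458 = 147 unsafe.
- 40% admitted: 3615 × 0.40 = 1446 admissions, 2169 discharges; 0.06 × 2169 = 130 unsafe.
- As a share of visits: 147/3615 = 4.1% and 130/3615 = 3.6%.

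**Avoidable admissions.** 0.20 × 1157 = 231 at the lowest; 0.29 × 1446 = 419 at the highest.

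**Change in admissions with a perfect model** (all returns in the year-10 data, model also admits at the return).

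| Admitted | Unnecessary | By episode | By visit |
|---|---|---|---|
| 32% | 20% | −231 | −231 + 147 = −84 |
| 32% | 29% | −335 | −335 + 147 = −188 |
| 40% | 20% | −289 | −289 + 130 = −159 |
| 40% | 29% | −419 | −419 + 130 = −289 |

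The excess is one admission per unsafe discharge caught. At an assumed sensitivity of 0.8 for unsafe discharges it is 0.8 × 130 = 104 to 0.8 × 147 = 118.

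**Imperfect specificity** (assumed 0.9; 32% admitted, 29% unnecessary, all unsafe discharges caught). Unnecessary admissions avoided: 0.9 × 335 = 302. Safe discharges wrongly admitted: 0.1 × (2458 − 147) = 231. By episode: −302 + 231 = −71. By visit: −71 + 147, about +77 before rounding. In this scenario the sign changes.

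**Cost of one caught unsafe discharge** (illustrative units: ED visit 1, admission 5).
- Correct: current care 1 + 5 = 6, model 5, difference −1.
- First row carries only its own visit: current care 1 + 5 = 6, model 5 + 5 = 10, difference +4. The sign is wrong.
- First row already includes the return stay: current care 6 + 5 = 11, model 5 + 5 = 10, difference −1. The difference is right, but both totals count the return stay twice. The return row adds a zero difference, so about 4% of the pairs in the log-cost test are linked rows that dilute the mean.

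**Against the primary criterion** (log cost lowered by at least 0.10 SD), only on the excluding reading, for a perfect model with two cost levels, taking the SD of actual log cost. The effect is (avoidable − unsafe)/3615 ÷ √(p(1 − p)), where p is the admission rate; the cost ratio cancels. At 32%/20%: (231 − 147)/3615 = 0.023; √(0.32 × 0.68) = 0.466; effect 0.05 SD. The others are 0.11 (32%/29%), 0.09 (40%/20%) and 0.16 (40%/29%). Two of the four fall below 0.10. By episode, with admission cost 5 or 10, the effect is 0.14 to 0.25 SD.

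**The case against.** The strongest reply is that the article never says the return row is kept. That is inferred from the absence of a removal step, and a journal article may leave visit linkage to a fuller document. The worked example also points towards linkage: it attaches the early return and the cost of an unsafe discharge to the first visit, and ED returns are to be computed from the interval that defines unsafe discharge. If the return admission were credited to the first row as well, each row would show one admission in both arms and nothing would be added.

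Part of this stands. The ED-return outcome is less affected, and reading the cost of an unsafe discharge as including the return stay is the more natural choice, because the example uses that cost to price a discharge together with its return. For admissions the reply does not work. The plan compares the model's prediction with the actual disposition, and the actual disposition at the first visit was discharge. Crediting an admission to that row contradicts the stated comparison.

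A reader might infer that the cost result is wrong, that 31% (130/419) to 64% (147/231) of the benefit will be hidden, or that the simulation cannot answer Aim 3. The document does not support these. The raw cost difference is correct if the return stay is included. The percentages are ceilings for a perfect model on a secondary outcome. The cost and ED-return comparisons can still be informative. Nor could this bias create a false claim of fewer admissions. An error in the other direction is possible if a wrongly discharged necessary admission is counted as an avoided one, although the assumed unsafe discharge implies a return with admission.

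**Conclusion.** The point holds for the admissions comparison as written. With the visit as unit, four groups summed and no removal step, each unsafe discharge that the model catches adds one admission that the episode does not have. The excess is at most about 130 to 147 admissions, against 231 to 419 avoidable ones. This rests on the literature rates, on returns falling within year 10 and the same health system, and on the model also admitting at the return; the excess scales with the share of unsafe discharges caught. The bias is on a secondary hypothesis and runs against the model.

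For the primary cost outcome the point is conditional. The contrast is distorted in the same way only if an unsafe discharge's cost excludes the return stay. Otherwise what remains is double-counted totals and about 4% linked rows in the paired test. Because this accounting choice could decide the 0.10 SD criterion, it should be settled before year-10 results are seen.

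**What to change.** - Make the Aim 3 unit the episode: the first ED visit plus any linked return visit and admission within the return threshold. Give each episode one cost, one admission indicator and one ED-return indicator, and do not enter linked returns as separate rows.
- When the model admits at the first visit, remove the linked return and its cost.
- Count a necessary admission that the model wrongly discharges as a return with admission, not as an avoided admission.
- State that the cost of an unsafe discharge includes the return stay.
- Run the paired t-test and McNemar's tests on episodes.

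The cost is linkage of visits already in the data set and a rewording of the simulation step. On the rates above, units fall from 3615 to about 3615 − 147 = 3468 or 3615 − 130 = 3485, still far above 857.
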